## Abstract

**Introduction:**

Specific phobias (intense, enduring fears of an object or situation that lead to avoidance and severe distress) are highly prevalent among children and young people. Cognitive–behavioural therapy (CBT) is a well-established, effective intervention, but it can be time consuming and costly because it is routinely delivered over multiple sessions during several months. Alternative methods of treating severe and debilitating phobias in children are needed, like one-session treatment (OST), to reduce time and cost, and to prevent therapeutic drift and help children recover quickly. Our study explores whether (1) outcomes with OST are ‘no worse’ than outcomes with multisession CBT, (2) OST is acceptable to children, their parents and the practitioners who use it and (3) OST offers good value for money to the National Health Service (NHS) and to society.

**Method:**

A pragmatic, non-inferiority, randomised controlled trial will compare OST with multisession CBT-based therapy on their clinical and cost-effectiveness. The primary clinical outcome is a standardised behavioural task of approaching the feared stimulus at 6 months postrandomisation. The outcomes for the within-trial cost-effectiveness analysis are quality-adjusted life years based on EQ-5D-Y, and individual-level costs based of the intervention and use of health and social service care. A nested qualitative evaluation will explore children’s, parents’ and practitioners’ perceptions and experiences of OST. A total of 286 children, 7–16 years old, with DSM-IV diagnoses of specific phobia will be recruited via gatekeepers in the NHS, schools and voluntary youth services, and via public adverts.

**Ethics and dissemination:**

The trial received ethical approval from North East and York Research Ethics Committee (Reference: 17/NE/0012). Dissemination plans include publications in peer-reviewed journals, presentations in relevant research conferences, local research symposia and seminars for children and their families, and for professionals and service managers.

**Trial registration number:**

ISRCTN19883421; Pre-results.

Strengths and limitations of this studyTo our knowledge, this is the largest proposed treatment study and economic evaluation of interventions for childhood phobias to date.Interventions are delivered by multidisciplinary professionals working in multiple sectors including health, education and voluntary organisations.Children with all types of specific phobias and different learning abilities are included.There are no midpoint outcomes; therefore, the study cannot tell whether children improve with one-session treatment quicker than with multisession therapy or how the two interventions may work in different ways to change outcomes (mechanisms of action). However, the study includes longer term outcomes which are useful in evaluating sustained effect, if any, of the intervention.

## Introduction

A specific phobia is an intense, enduring fear of an identifiable object or situation that leads to distress and avoidance.^1^ It is estimated that between 5% and 10% of children have a specific phobia severe enough to impact on their everyday functioning,^2^ but fewer than 10% seek treatment, therefore, the average duration of phobias is 20 years.^3^ The psychological, developmental and medical impact of these phobias is significant, with higher rates of health service usage than most other anxiety disorders.^4^ Phobias in children can result in considerable academic difficulties,^5^ personal distress^6^ and interference in day-to-day activities.^7^ Cognitive– behavioural therapy (CBT) is the dominant therapeutic intervention for specific phobias^8 9^ within health services in the UK. Robust evidence supports the efficacy of CBT for anxiety disorders in general,^10–12^ and for specific phobias in particular; however, CBT can be time consuming, costly and difficult to access because it is delivered over multiple sessions during several weeks or months by therapists that have received lengthy training.^13–16^

Alternative methods of CBT delivery, like one-session treatment (OST),^17^ can be used to reduce demands on therapist time and associated costs, prevent therapeutic drift, and ultimately help children recover quicker.^18 19^ OST is a variant of CBT, delivered in a single 3-hour session. A central feature is graded exposure where the subject comes into proximity with the phobic stimulus in a series of graduated steps (from the easiest to the most difficult). For example, graded exposure for a phobia of dogs might first involve looking at pictures of dogs, followed by videos of dogs, then by observing dogs in a local park at a distance and finally by interacting with dogs first hand. OST has been shown to be clinically effective in children.^20–22^ For example, Ollendick *et al*
20 randomised 196 children (ages 7–16) with phobias to one of three groups: (1) OST, (2) an education support group or (3) a wait-list control group. OST was superior to both comparators as measured by improved phobia severity, percentage of children who were diagnosis free, and child-related and parent-rated anxiety and treatment satisfaction postintervention and at 6 months follow-up. However, to our knowledge, OST has not been compared with the current ‘gold-standard’ approach to specific phobias (ie, CBT), and has not been trialled in the UK within the National Health Service (NHS).

The present research is a non-inferiority, parallel group randomised controlled trial comparing the clinical and cost-effectiveness of OST versus CBT for specific phobias in children and young people ages 7–16 years old. The primary aim is to test whether OST is non-inferior (ie, produces similar clinical benefits) to multisession CBT in helping children with their specific phobia(s), and the wider impact their phobia(s) have on mental health and quality of life. A nested qualitative evaluation will explore whether OST is acceptable to children, their parents and the practitioners who deliver OST. Finally, an economic evaluation will examine whether OST offers good value for money to the NHS and society compared with multisession CBT.

### Design

This is a non-inferiority randomised controlled trial that compares clinical outcomes of OST with those of multisession CBT at 6 months postrandomisation. Nested within this trial is an economic evaluation of the cost-effectiveness of OST against CBT for outcomes and costs over 6 months. Interviews evaluate perceptions and experiences of OST by children, parents and practitioners also at 6-month follow-up. An internal 9-month pilot determines feasibility of recruitment and retention, and monitors the occurrence of any adverse events.

### Recruitment

Our recruitment strategies follow routine care pathways for children with specific phobias. These pathways differ across our participating sites, which include NHS Trusts, Local Authorities and voluntary agencies across England. We have mapped the care pathways in each geographical area and we promote the study within teams of professionals who routinely receive referrals of children with specific phobias, such as Child and Adolescent Mental Health Services (CAMHS), Children’s Hospitals, youth services and schools. We also draw attention of the study to potential participants through public adverts, for example, in local newspapers and posters in general practitioner (GP) surgeries.

### Randomisation

Following written consent and completion of the baseline measures, random allocation to treatment groups is carried out remotely through a secure web-based programme designed by the Sheffield Clinical Trials Research Unit (CTRU). The randomisation allocation ratio is 1:1 to facilitate equal sample sizes across both the OST and CBT groups. Randomisation is stratified according to two age groups (7–11 years old vs 12–16 years old) and two phobia severity groups (mild to moderate vs severe); we use random permuted blocks of variable size to ensure enough participants are allocated evenly to each arm of the trial within each stratum.

### Blinding

Complete concealment of allocation, ‘blinding’, from both participants and researchers in studies of psychological interventions is often extremely difficult, and, at times, impossible.^23–26^ Our study takes a number of steps to facilitate blind assessment of outcomes as a way of reducing bias. First, the research assistants collecting baseline and follow-up outcomes are independent of the practitioners delivering the interventions. Second, the research assistants are not informed of the participants’ group allocation and are not involved in the therapy sessions. Participants are explicitly reminded not to disclose to the research assistant their allocated group. In the event of these procedures being compromised (eg, a research assistant learning the participant’s allocated group), we record this and arrange for a different outcome assessor in the future wherever possible. The trial statisticians and health economists are blind to treatment allocation while the trial is ongoing.

### Interventions

#### One-session treatment

OST is a variant of CBT, but rather than being delivered in weekly 45–60 min sessions as in conventional CBT, OST is delivered in a longer single session (approximately 3 hours). Prior to the single session, a 1-hour assessment/planning session takes place during which the practitioner carries out an assessment in order to plan the treatment session. This involves:Determining the nature, history and associations of the phobia.Determining any maintaining factors for the phobia (eg, what the child avoids, what safety behaviours she/he engages in, how friends and family may collude with the phobia).Collecting information about the child’s cognitions including catastrophic thoughts (eg, what do you think may happen if…, what goes through your mind when you…).Generating a fear hierarchy (ie, a ‘ladder’ of situations or objects that the child avoids because of their phobia, in the order of the fear or anxiety evoked, starting from the least frightening).Explaining what is involved in treatment and that the exposure tasks are graded and negotiated in every step of the way and that nothing will ever happen without the child’s permission.

The single session combines graded exposure, participant modelling, reinforcement and cognitive challenges. The main principle of graded exposure is that the child gradually confronts the situations from their fear hierarchy and remains in each situation until their anxiety/fear subsides at least by 50%. In participant modelling, the therapist first demonstrates to the child how to interact with the phobic object and then helps the child gradually approach the phobic object by joint approaches with the therapist gradually fading involvement. Reinforcement from the therapist may take the form of social praise, encouragement. Finally, the therapist uses the exposure tasks as means for actively eliciting, challenging and testing negative cognitions or catastrophic thoughts associated with the feared situation and by promoting positive cognitions in phobic situations. It is important that the child maximises, maintains and generalises their gains from graded exposure by practising self-directed and parent/carer supported exposure tasks at home for the ensuing weeks. Maintenance tasks include a commitment to refrain from avoiding or escaping from feared situations and to deliberately engineer or enter a feared situation regularly.

#### Cognitive–behavioural therapy

CBT helps people to change unhelpful beliefs and behaviours arising in feared situations, such as catastrophic thinking and safety behaviours. Interventions based on CBT are the dominant model of treatment for specific phobias, and are supported by a robust literature attesting to its efficacy.^8–12^ CBT interventions are often delivered in 45–60 min sessions every week or fortnight over several weeks or months. Each CBT session takes the form of structured discussions with a therapist, has a specific agenda and sets homework tasks for the child or young person between sessions. CBT for children and young people with specific phobias aims to help the child/young person to: (1) recognise anxious feelings and bodily reactions to anxiety; (2) gradually confront their feared situations until their anxiety subsides; (3) capture and challenge anxious thoughts when faced with a phobic situation or object; (4) challenge avoidance behaviours, or behaviours that maintain or reinforce the phobia and (5) develop coping strategies and anxiety management techniques if distress and physical responses to anxiety are overwhelming. There is no recommended number of CBT sessions for specific phobias but it can vary between 4 and 20 sessions.

### Fidelity to the interventions

Practitioners responsible for specific phobia treatment across the recruiting centres will be trained in OST during a day’s workshop, with senior practitioners (eg, trained therapists) attending a modified half-day training on OST and a half-day training on supervising and training others in OST to be able to offer continuous support and supervision to junior colleagues. OST and CBT sessions are audio recorded whenever possible with consent from the child and parent. A random selection of 15% of participants at each site (or the nearest whole number) has one of their sessions (whether OST or CBT) reviewed by a supervisor at quarterly intervals. Supervisors score the recorded sessions to assess therapist fidelity to OST and CBT using the OST Rating Scale 27 and the CBT Scale for Children and Young People,^28^ respectively. This is to make sure that CBT principles are applied in both treatment arms. These are used in supervision to improve fidelity to the intervention and address training needs for the therapists as per usual practice.

### Outcome measures

We are collecting demographic information (eg, age, gender, etc) from all children/young people and their parents. Children and parents are also asked if they have a treatment preference at baseline, although this does not affect their randomisation in any way. Participants complete the following measures at baseline and then at 6 months follow-up.

#### Behavioural avoidance task

The primary outcome is the behavioural avoidance task (BAT) at 6 months postrandomisation. The BAT is a widely used measure of treatment outcomes for phobias in children.^6 21^ The BATs for the Alleviating Specific Phobias Experienced by Children Trial (ASPECT) trial are standardised for each stimulus and have been found to have good test–retest reliability^20 29^ and strong correlation with other outcome measures of anxiety and phobia.^30 31^ During a BAT, the child gradually confronts their phobic stimulus over 10 predefined steps of increasing difficulty; the child does not have to complete all the steps. For example, a child with spider phobia may start the BAT at step 0, standing outside of a room that has a spider contained in a box. Subsequent steps the child may take are: opening the door (step 1), passing through the doorway (step 2), through to holding the spider for 20 s (step 10). The number of steps the participant takes is the main unit of measurement recorded for analysis. The BAT also includes a measure of subjective units of distress whereby the child reports their level of fear at the start of the BAT, and at the last step completed (ranging from 0=no fear at all to 8=extreme fear).

#### The anxiety disorder interview schedule for children and parents

Anxiety disorder interview schedule (ADIS)^32^ is a well-established semistructured interview^3 32 33^ that obtains information from both the child and their parent/carer about the type of specific phobias experienced (eg, animal/insect, small spaces, blood/injection phobias, etc), the degree of associated fear (rated from 0=not at all to 8=very, very much), whether the phobia causes avoidance (rated as ‘yes’ or ‘no’) and interference with daily life (rated from 0=not at all to 8=very, very much).

#### Child Anxiety Impact Scale for children and parents

The Child Anxiety Impact Scale for children and parent (CAIS-C/P)^34^ collects information as to what extent feeling ‘nervous, anxious or afraid’ impacts on the daily life of the child. The child and the parent independently rate, on a 4-point scale ranging from 0=not at all to 4=very much, 27 statements grouped in 3 subdomains: school activities (eg, getting to school on time in the morning), social life (eg, making new friends) and home/family life (eg, getting ready for bed at night).

#### The Revised Children’s Anxiety and Depression Scale

The Revised Children’s Anxiety and Depression Scale-C/P (RCADS-C/P)^35–38^ comprises 47 items to capture separation anxiety disorder, social phobia, generalised anxiety disorder, panic disorder, obsessive compulsive disorder and major depressive disorder. Children state the frequency of which statements such as ‘I worry about things’, I have trouble sleeping’ and ‘I feel I will make a fool of myself in front of people’ relate to them on a 4-point scale: 0=never, through to 1=sometimes, 2=often and 3=always.

#### EQ-5D-Y

The EQ-5D-Y, originally developed by the EuroQoL group,^39–41^ is a widely used measure of health-related quality of life in children and young people. Children and young people are able to classify their own health on a 3-point scale, 1=no problems, 2=some problems and 3=a lot of problems, over five dimensions: mobility (walking about), looking after myself, doing unusual activities, having pain or discomfort and feeling worried, sad or unhappy. Additionally, the EQ-5D-Y includes a Visual Analogue Scale where participants can indicate their overall health status from 0 (worst imaginable state) to 100 (best imaginable state). All questions refer to the participant’s health state ‘today’.

#### Child Health Utility 9D

The Child Health Utility 9D (CHU-9D) is a health-related quality of life measure validated for children and young people.^42 43^ Participants select a sentence from a possible five to describe how they feel today in relation to a number of constructs (ie, sadness, tiredness, pain, etc). For example, participants are asked to select one of five statements that best reflects how worried they feel ranging from ‘I don’t feel worried today’ to ‘I feel very worried today’.

#### Goal-based outcome measure

A goal-based outcome measure is a method of comparing how far a participant feels they have moved towards reaching a specific goal they have set before the intervention has begun. A goal-based outcome measure based on recent guidelines^44^ will be used to set up to three goals at baseline, with progress towards meeting these goals rated on a 10-point scale at the 6-month follow-up point. Progress can range from 0 (ie, goal not met), to 5 (ie, halfway to reaching the goal), through to 10 (ie, goal reached). For example, a participant with a dog phobia may set as their goal that they would like to be able to spend teatime at their grandmother’s house where there is a dog.

#### Resource Utilisation Questionnaire

We developed a bespoke questionnaire to assess use of healthcare and other resources, based on a previous Resource Utilisation Questionnaire by Barrett and colleagues^45^ and its adaptations for younger populations by members of our research team^45–47^ The questionnaire is completed by the parent and collects data on resource and service utilisation relating to the child over the previous 6 months on: general health and community service use (ie, appointments with GP’s, nurses, social services and educational services); mental health service use (ie, appointments with a psychiatrist, psychotherapists, psychologists, CAMHS therapists and other forms of mental health support); hospital-based services (ie, visits to A&E, urgent care centres and hospital stays); days missed from school by the child; days missed by parents/carers from work or studies.

### Statistical analysis

#### Sample size

The proposed sample size and non-inferiority margin are based on two separate Cochrane reviews looking at the effects of psychotherapy for those experiencing anxiety. First, Wolitzky-Taylor *et al*
47 conducted a review on studies that used both observer-rated BAT-like assessments and self-report questionnaires on adults with specific phobias and reported an overall, large effect size of d=0.81. However, as the treatment may have a different effect on children, we also examined the review of Reynolds *et al*.^48^ This review was conducted on studies of children with specific phobias but used self-report questionnaires rather than observer-rated BATs. The review reported a large effect size (d=0.85) for multisession CBT. Prior meta-analyses suggest that a standardised mean difference of around 0.8 on the BAT scale is clinically important. Therefore, we set the non-inferiority margin to be half of this at 0.4.^49^ Assuming a correlation of 0.5 between baseline and final BAT measure, we would require 200 participants (100 in each arm) to have 90% power with a 2.5% one-sided significance level to demonstrate non-inferiority of OST compared with CBT. The therapy is delivered by therapists who will see approximately 15 patients each and we anticipate a weak therapist effect (intraclass correlation coefficient=0.01). This clustering will lead to a design effect of 1.14 which increases the number required per arm to 114. We further assume a 20% drop-out rate suggesting that total number of 286 children and young people (143 per arm) will need to be recruited to the study to demonstrate non-inferiority of OST compared with CBT.

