#### Data analysis

As this trial follows a randomised, parallel group, non-inferiority design, data will be analysed and reported according to both Consolidated Standards Of Reporting Trials (CONSORT) guidelines^50^ and the non-inferiority trials CONSORT extension.^51^ Baseline data, including demographic characteristics (eg, age, gender) and clinical measures (eg, BAT, RCADS), will be reported between the two randomised groups. Jones *et al*
49 recommend both per-protocol and intention-to-treat (ITT) analyses for non-inferiority designs. For an equivalence or non-inferiority trial, as opposed to a comparative trial, ITT analyses are not considered conservative, as any blurring of the difference between the treatment groups increases the chance of declaring equivalence. We follow this recommendation with the refinement that the main analysis of the primary outcome will be per protocol (or completers only) with a sensitivity analysis on the ITT population.^49^ We will require both the per-protocol and ITT analyses to demonstrate conclusive evidence to declare that OST is ‘non-inferior’ to multisession CBT. If the results of the analysis are discrepant (eg, the ITT rejects the null of inferiority but the per-protocol analysis does not or vice versa) then we will report the conflicting results from both analyses highlighting the inconclusive nature of the results. For the sake of the analysis, a participant in the OST group is defined as per protocol if they attend both the initial functional assessment and the rapid exposure therapy session. A participant in the CBT group is defined as per protocol if they attend at least four CBT sessions.

The primary outcome (mean BAT score at 6 months) and the secondary outcomes (ADIS, CAIS, EQ-5D-Y, CHU-9D, RCADS and goal-based outcome scores) will be compared between groups using mixed-effects linear regression with exchangeable correlation to allow for the clustering of outcomes within therapist. The analysis will be conducted controlling for baseline BAT score, site and stratifying variables (age group and baseline phobia severity). The null hypothesis of inferiority will be rejected if the two-sided 95% CI for the difference is wholly below 0.4 (the range of clinical non-inferiority).

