## Ethics and dissemination

### Obtaining informed consent from participants

As all participants in this study are aged 16 or under, consent is required from both a person with parental responsibility, and the participant themselves if they are deemed competent to do so. Where a child is not deemed competent to give full informed consent, we take parental consent and seek assent from the child. Prior to the consent meeting, the parents and the children receive information about the study and have the opportunity to discuss any questions or concerns with members of the research team. Two age-specific versions of the child information sheets are available: one for those aged 7–11 years and one for those aged 12–16 years. All information leaflets and consent forms are codeveloped by the research team and PPI representatives to ensure acceptability among participants. If a participant wishes to withdraw from their allocated intervention, we check whether they are still agreeable to participate in the planned follow-up assessment at 6 months, so that their outcomes can be included within our ITT analysis.

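### The stated 90% power is for a single analysis, and holds for the both-analyses success rule only if the 20% drop-out allowance also covers attendance-based per-protocol exclusions

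*Protocol article*

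**What the plan says.** The Sample size section fixes the margin ("Therefore, we set the non-inferiority margin to be half of this at 0.4") and then the base number: "Assuming a correlation of 0.5 between baseline and final BAT measure, we would require 200 participants (100 in each arm"). The power attached to that number is stated for one comparison: "to have 90% power with a 2.5% one-sided significance level to demonstrate non-inferiority of OST compared with CBT". It adds clustering, with "therapists who will see approximately 15 patients each and we anticipate a weak therapist effect (intraclass correlation coefficient=0.01"), giving a design effect of 1.14 and 114 per arm. A single allowance for losses follows: "We further assume a 20% drop-out rate suggesting that total number of 286 children and young people (143 per arm"). The section mentions neither the analysis sets nor the success rule.

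Both are set in the Data analysis section. The "main analysis of the primary outcome will be per protocol (or completers only) with a sensitivity analysis on the ITT population". A child is per protocol by attendance: both OST appointments, or at least four CBT sessions. The success rule for a claim of non-inferiority begins: "We will require both the per-protocol and ITT analyses to demonstrate conclusive evidence to declare that OST is". If the two analyses disagree, both are reported and the result is called inconclusive.

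Two other places bear on what drop-out means. The missing-data paragraph of the Data analysis section couples drop-out with attrition and treats the consequence as missing data. The section on obtaining informed consent says: "If a participant wishes to withdraw from their allocated intervention, we check whether they are still agreeable to participate in the planned follow-up". The stated purpose is to keep those children's 6-month data in the ITT analysis.

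**The concern.** The power figure and the decision rule are not tied to each other. After a 20% loss the trial has the 114 per arm that one analysis needs for 90% power, with almost nothing in reserve. The main analysis, however, leaves out any child who did not meet the attendance rule, including children who did have a 6-month BAT. If those children are lost in addition to the 20%, the per-protocol analysis falls below the planned size, and the chance that both analyses succeed is lower still.

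At stake is how likely the trial is to end with the inconclusive verdict that the plan provides for when the analyses disagree. There is also a practical problem. Because the 20% is not defined, the DMEC cannot tell whether 20% missing BATs plus some non-attendance is within plan or beyond it.

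**Working it through.** **Inputs.** From Sample size: margin 0.4 SD; baseline-final correlation 0.5; one-sided 2.5%; power 90%; 15 patients per therapist; intraclass correlation 0.01; drop-out 20%. From Randomisation: 1:1 allocation. Assumed here, because the article gives no figure: the further per-protocol exclusion rate x, equal in both arms; a true difference of 0 in both analysis sets; design effect held at 1.14; no material gain in information from multiple imputation.

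**Step 1: reproduce the plan's figure.**
- Variance after baseline adjustment: 1 − 0.5² = 0.75.
- n per arm = 2 × 0.75 × (1.960 + 1.282)² / 0.4² = 98.5, so 99 by the normal approximation. With the t distribution, 100 per arm gives 90.1%, which matches the stated 100.
- Design effect = 1 + (15 − 1) × 0.01 = 1.14; 100 × 1.14 = 114.
- 114 / 0.8 = 142.5, so 143 per arm and 286 in total. The chain reproduces.

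**Step 2: power left after the 20% loss.** The effective number per arm is 143 × 0.8 / 1.14 = 100.4. Power = Φ(0.4 / √(1.5 / 100.4) − 1.96) = Φ(1.31) = 90.5%.

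**Step 3: exclusions on top of the 20%.** Effective per-protocol n = 100.4 × (1 − x), put into the same formula. For joint power, the per-protocol set is nested in the ITT set, so the two test statistics are taken as bivariate normal with correlation √(1 − x). Total per-protocol loss is 1 − 0.8(1 − x).

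| Further exclusion x | Total per-protocol loss | Per-protocol n per arm | Correlation | Per-protocol power | Joint power |
|---|---|---|---|---|---|
| 0% | 20% | 114.4 | 1 | 90.5% | 90.5% |
| 5% | 24% | 108.7 | 0.975 | 89.0% | 88.1% |
| 10% | 28% | 103.0 | 0.949 | 87.4% | 86.2% |
| 20% | 36% | 91.5 | 0.894 | 83.3% | 82.1% |

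The last two columns differ by 0.9 to 1.2 points wherever x is above 0. That gap is the cost of requiring both analyses. The rest of the fall comes from the exclusions.

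**Step 4: the other reading, with the 20% covering all per-protocol loss.** Per-protocol power stays at 90.5%. If ITT then loses between 0% and 20%, ITT power is 95.5% down to 90.5%, and joint power lies between 89.6% and 90.5%.

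**Step 5: milder assumptions.**
- If the design effect shrinks as fewer children per therapist are analysed, 1 + (15(1 − x) − 1) × 0.01, per-protocol power is 87.8% at x = 10% and 84.3% at x = 20%; joint power is 86.7% and 83.0%.
- If exclusions arise only in the CBT arm, per-protocol power is about 89% at x = 10% and 87% at x = 20%.

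**The case against.** The strongest reply is that the article never says the 20% means a missing BAT. It glosses the per-protocol set as completers, so drop-outs can be read as non-completers and 114 per arm as the per-protocol number. Step 4 shows that the stated 90% then holds. This stands, and it is why the point is conditional. It does not remove the point: the article's own use of drop-out in the missing-data paragraph, and its follow-up of children who leave treatment, favour the other reading.

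A reader might infer that the design flatly fails to deliver 90%, or that 286 was miscalculated. The documents support neither. The first needs an exclusion rate that the article does not give, on top of a full 20% loss; the second is ruled out by Step 1. A reader might also blame the both-analyses rule, but it costs only about 1 point because the two estimates are highly correlated.

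Other replies hold in part:
- Per-protocol status depends on attendance alone, and multiple imputation is planned in both sets, so attenders without a BAT stay in the per-protocol set. The n in the table counts observed BATs. Imputation may add a little information, but it does not bring back children excluded for non-attendance.
- Power by exclusion rate is detail that a condensed article may leave to the full protocol or SAP. Here, though, the article itself states the power, the main analysis set, the attendance rule and the success rule, and the first is not matched to the others.
- Lost power adds no risk of a false claim of non-inferiority, and the internal pilot already checks retention. Both are true, and they limit how serious the point is.

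**Conclusion.** The point holds in conditional form. The 90% applies to the trial's decision rule only when total per-protocol loss, from missing BATs and non-attendance together, is 20% or less. If attendance-based exclusions come on top, which is the more natural reading, 5% to 20% further exclusion takes joint power to about 88% down to 82%. These figures rest on the assumptions listed with the inputs; Step 5 shows that relaxing two of them reduces the shortfall but does not remove it. What needs correcting is what the power figure is said to cover; the sizing arithmetic is sound.

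**What to change.** 1. State which losses the 20% is meant to cover.
2. Restate the power for the rule as written: per-protocol power and joint per-protocol-and-ITT power over a range of further exclusion rates starting at 0%, with the assumptions given.
3. State that the 90% applies only when total per-protocol loss is 20% or less.
4. Have the DMEC track missing BATs and attendance-based exclusions together against that figure.

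The sample size of 286, the attendance definitions and the success rule can all stay as they are. The cost is a slightly less favourable stated power and one more quantity in the monitoring reports; no extra children are needed.
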